#### Methods for Any Additional Analyses

The main analysis will be on the whole study population. Additional analyses will be stratified by type of intervention. Also, analyses will consider uterus volume as a proxy for complexity of surgery.

#### Blinding

Anesthesiologist and surgeon will be aware of the treatment assignment. The patient, the nurse who will assess the primary outcome (NRS on day 1), and the statistician will be blinded.

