**Methods:**

In this multicenter, randomized controlled trial with a superiority design, 300 patients will be randomly allocated in the ratio 1:1 to moderate neuromuscular blockade with a target insufflation pressure of 12 mm Hg or deep neuromuscular blockade with a target insufflation pressure of 8 mm Hg, with stratification by type of surgery and clinical center. The patient, the statistician, and the nurse who will assess the primary endpoint will be blinded to the allocation.

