### Randomization: Sequence Generation, Allocation Concealment Mechanism, and Implementation

#### Sequence Generation

Allocation sequence to groups A and B will be obtained using the “ralloc” module in Stata 14 (StataCorp LLC, College Station, Texas), with blocks of variable size (4-6-8), and stratified by participating center and type of surgery (hysterectomy). The algorithm for sequence generation will be maintained by the study statistician and will not be communicated to any additional study staff.

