#### Allocation Concealment Mechanism

The study statistician will prepare the appropriate number of numbered, opaque, sealed envelopes for each center. These will be maintained at each center by an appropriately trained research nurse. At the time of anesthesia induction, the surgical nurse will open the relevant envelope, and the anesthesiologist will proceed to the allocated treatment.

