### Statistical Analysis

#### Statistical Methods for Analyzing Primary and Secondary Outcomes

The primary endpoint (AUC for pain) will be compared by Student *t* test. *P* value <.05 will be considered significant. Descriptive statistics will be obtained for all variables assessed in the study population. Mean and SD will be used for normally distributed variables, and mean and interquartile range will be used for skewed distributions and proportions for categorical variables. Whenever relevant, 95% CIs will be calculated.

For group comparisons, Student *t* test (rank-sum test or Mann–Whitney test for skewed distributions) will be used for quantitative variables (analysis of variance or Kruskal-Wallis for >2 groups, respectively) and Pearson chi-square test (Fisher exact test where appropriate) for categorical variables. Two-tailed tests will be used in all cases. *P* value <.05 will be considered significant.

Generalized mixed models will be used to assess differences between groups in endpoints measured at several time points.

A detailed statistical analysis plan will be developed after the first 40 patients have been enrolled.

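### The protocol lists the statistician as blinded, yet gives the only statistician role it describes the allocation algorithm and the envelopes

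*Protocol article*

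**What the plan says.** Two places in the protocol article claim that the statistician is blinded:

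- Abstract, Methods: "The patient, the statistician, and the nurse who will assess the primary endpoint will be blinded to the allocation".
- Blinding: "The patient, the nurse who will assess the primary outcome (NRS on day 1), and the statistician will be blinded".

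Two other places describe what the statistician does:

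- Sequence Generation: "The algorithm for sequence generation will be maintained by the study statistician and will not be communicated to any additional study staff".
- On the envelopes, the Allocation Concealment Mechanism section says: "The study statistician will prepare the appropriate number of numbered, opaque, sealed envelopes for each center".

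The sequence itself is described in the passive: "Allocation sequence to groups A and B will be obtained using the “ralloc” module in Stata 14". The Discussion adds that generation is central, but names nobody.

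On the timing of the analysis plan, the section on statistical methods for primary and secondary outcomes says: "A detailed statistical analysis plan will be developed after the first 40 patients have been enrolled". It gives no author, no lock point and no condition on what the author may have seen. The same section already fixes the main test: "The primary endpoint (AUC for pain) will be compared by Student *t* test". The Interim Analysis section plans none.

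**The concern.** Whoever keeps the algorithm and fills numbered envelopes can link each envelope number to an arm. A person in that position is not blinded to allocation unless some separation of duties is described, and the article describes none. It claims blinding for three parties only, and one of the three claims conflicts with its own account of randomisation.

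At stake is how far a reader can rely on the analysis having been specified and carried out without knowledge of arm. The surgeon and the anesthesiologist are openly unblinded, so the remaining protections carry more weight. The timing of the analysis plan adds a secondary point. Writing it during recruitment is acceptable if the author is blind to outcomes by arm, but here the text does not secure that.

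**Working it through.** The point is one of consistency, so the check sets the sections side by side. The sample-size figures do not enter it.

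**Step 1. Is the key holder the role that is declared blinded?**

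- Declared blinded: the statistician (Abstract, Methods; Blinding).
- Keeps the algorithm, with no one else told: the study statistician (Sequence Generation).
- Prepares the envelopes for each center: the study statistician (Allocation Concealment Mechanism).
- Any second, independent or unblinded statistician: none mentioned.

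Only one statistician role appears, always with the definite article. Read naturally, the role that holds the key is the role declared blinded, and both statements cannot be true of it. That a single person both holds the key and analyses the data is an inference from the role names; the article does not say so outright.

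**Step 2. Which blinding claims are affected?**

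Only the statistician's. Nothing in the two randomisation sections gives the patient or the assessing nurse access to the algorithm. Concealment at entry is not impaired either: the envelopes are opaque and sealed, they are opened at induction, and the statistician is given no part in enrolling or treating patients.

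**Step 3. How far has recruitment gone when the analysis plan may be started?**

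- Inputs: 40 patients (section on statistical methods) and 300 planned (Sample Size Calculation).
- Fraction enrolled at the earliest start = 40/300 = 0.133, or 13.3%.

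This is an enrolment fraction. It does not measure outcome data seen by anyone, and the article describes no release of data at that point.

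**Step 4. What is still open when the plan is written?**

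- Largely fixed: the pain AUC over 24 hours, its seven scheduled readings plus those at rescue requests (Primary Outcome), and the Student t test at the 5% level.
- Open: the analysis set. Secondary Outcomes removes procedures longer than 90 min from the analysis, whereas Methods for Any Additional Analyses bases the main analysis on everyone in the study. The analysis plan has to reconcile the two. Sample Size Calculation expects at most 5% of patients to exceed the limit, that is 0.05 × 300 = 15 patients, leaving 300 − 15 = 285.
- Also open: the detail of the models for repeated and secondary endpoints, and the use of rank tests when those endpoints are skewed.

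The choice that touches the primary result most directly therefore concerns about 15 patients on the plan's own expectation. Those patients are defined after randomisation, by a duration that an unblinded surgeon can influence. This is the kind of choice that should be made blind to arm.

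**The case against.** The strongest reply is that the article may use one title for two people. A separate analyst could exist, and a condensed article may leave such detail to the full protocol. That is possible. However, the article states both halves itself, and as printed they do not fit together. This is a conflict in what is said, not a gap left to another document.

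Three stronger readings are tempting, and the documents do not support them.

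- **The trial's blinding fails as a whole.** It does not. The primary outcome is a patient's own rating collected by a blinded nurse. The Discussion rests its argument on the nurse and on concealment, not on the statistician.
- **The key holder writes the analysis plan.** The sentence on the plan is passive and names no author.
- **Analysis choices will follow the results.** No interim analysis is planned, dedicated data personnel collect the outcomes, and nobody is said to receive outcomes by arm at 40 patients. Knowing the key is not the same as seeing outcomes by arm. The primary endpoint is defined and its test is named without condition; the skewness rule comes in the next paragraph, on group comparisons generally.

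It is also fair to say that writing the plan after enrolment opens is no error in itself. The timing matters here only because the author's blindness is not secured.

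**Conclusion.** The concern holds in a limited form. As written, the protocol claims a blinded statistician while placing the algorithm and the envelopes with the only statistician role it describes, so that one safeguard is not in place. Patient and nurse blinding and allocation concealment stand.

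The secondary weakness is that the text does not ensure that the remaining analysis choices are made blind to arm, chiefly how the 90-minute exclusion fits with an analysis of everyone. No bias can be quantified from the documents, and there is no evidence that anyone will look at outcomes by arm. The 13.3% shows only how far recruitment may have gone at the earliest start of the analysis plan.

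The conclusion assumes that the two statistician labels denote one role. If a separate analyst exists and never has the key, the fault is one of wording only. Either way the sections need to be reconciled.

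**What to change.** - Assign sequence generation, envelope preparation and custody of the key until database lock to a named role already in the study organisation that neither analyses the data nor has access to outcome data. Staff who build or run the outcome database should not take this on if they can see outcomes, because that would put allocation and outcomes in the same hands.
- Give the analysing statistician coded arms only, and say so under Blinding.
- State that the detailed analysis plan will be finalised without access to outcome data by arm, with a signed and dated version. That plan should settle the analysis set.
- If the roles cannot be split, delete the statistician from the blinded parties in both the Abstract and the Blinding section.

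The cost is the reassignment of a one-off task plus a few sentences of text. The fallback costs only a slightly less favourable statement of blinding. Neither changes the design or the sample size.

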### Ethical Issues

This protocol, patient information sheet, and patient consent form have been reviewed and approved by the local ethics committee of Udine. All participating centers will obtain approval from their local ethics committee before starting enrollment. Italian law requires that approval is obtained first from the ethical committee of the coordinating center before obtaining approval from the other participating centers. Any protocol modifications will be submitted for review by each ethical committee. The study has been registered at Udine Ethical Committee (registration number: 23445/Ceur—4/9/2017). Written informed consent will be obtained directly from each patient by the participating anesthesiologist at the presurgery visit. Italian law does not allow consent from health care surrogates.

## Results

Recruitment to this trial is expected to open in June 2018 and is expected to close in June 2019.

## Discussion

Laparoscopic surgery provides benefits that include less bleeding, faster recovery, and shorter hospital stays. However, it is performed in a restricted space that may limit the surgeon’s view and range of motion. Higher CO_2_ insufflation pressure provides more insufflation volume [28] and improves surgical field visibility [29] but is associated with increased postoperative side effects [1]. During laparoscopic procedures, maintaining deep NMB, compared with moderate NMB, is associated with improved surgical conditions, as reviewed in Madsen and colleagues’ study [17]. NMB also improved surgical conditions when suturing the abdominal fascia [18]. However, the advantages of deep NMB in laparoscopic surgery are not well established, and questions remain regarding the clinical significance of the improvements, safety, and cost-effectiveness.

This study may confirm the reported benefits for postoperative pain and provide the additional data needed to address questions regarding the effects of this intervention on operating theater management and direct and indirect costs.

Strengths of this protocol include the large sample size and the participants being distributed among diverse institutions across the Italian territory, which will increase the generalizability of the results. The study will provide a comprehensive picture of the effect of and the collection and analysis of data on numerous secondary objectives, including an analysis of direct and indirect costs, to determine the overall effect of the intervention. Limitations include the possible introduction of bias because the surgeon and anesthesiologist will not be blinded to the intervention. However, potential bias will be reduced through blinding of the nurse who will assess the primary outcome (ie, the AUC of overall pain during the first 24 hours after surgery measured on an NRS of 0-10). Moreover, the randomization sequence will be generated centrally and allocation concealed in opaque, sealed envelopes until the time of anesthesia induction.

## Abbreviations

AUC: area under the curve
NMB: neuromuscular blockade
NRS: numerical rating scale
PACU: postanesthesia care unit
PONV: postoperative nausea and vomiting
PTC: posttetanic count
TOF: train-of-four
